## Abstract

**Background:**

During the last decade, twelve studies have been published investigating physical exercise interventions (PEIs) in patients with head and neck cancer (HNC) during radiotherapy (RT), chemoradiation (CRT) or bioradiation (BRT). These studies showed that these PEIs are safe and feasible. However, only two of these studies were randomised clinical trials (RCTs) with a satisfying sample size. Thereby, there is no cost-effectiveness study related to a PEI during RT, CRT or BRT ((C/B)RT) for patients with HNC. Therefore, the aim of this study is to investigate and compare physical performance, muscle strength, fatigue, quality of life (QoL), body mass index (BMI), nutritional status, physical activity, treatment tolerability, and health care related costs in patients with HNC with and without a 10 week PEI during (C/B)RT.

**Methods:**

This study, based on a trial within cohorts (TwiCs) design, will contain a prospective cohort of at least 112 patients. Fifty-six patients will randomly be invited for an experimental 10 week PEI. This PEI consists of both resistance and endurance exercises to optimize physical performance, muscle strength, fatigue, QoL, BMI, nutritional status, physical activity, and treatment tolerability of (C/B)RT. Measurements are at baseline, after 12 weeks, 6 months, and at 12 months. Statistical analyses will be performed for intention-to-treat and instrumental variable analysis.

**Discussion:**

This study seeks to investigate physical, QoL, and economic implications of a PEI. With a substantial sample size, this study attempts to strengthen and expand knowledge in HNC care upon PEI during (C/B)RT. In conclusion, this study is dedicated to provide additional evidence for PEI in patients with HNC during (C/B)RT.

**Trial registration:**

protocol was registered at clinicaltrials.gov with number NCT05988060 on 3 August 2023.

## Background

In 2021, the incidence of head and neck cancer (HNC) in the Netherlands was 3,174 and the prevalence was 10,635 [1]. HNC includes tumours located in four anatomical sites: pharynx, larynx, oral cavity, and sinonasal cavity [2]. The most prevalent causes of HNC are heavy consumption of tobacco and/or alcohol, and the human papillomavirus (HPV) [2].

Treatment of HNC by radiotherapy (RT), chemoradiation (CRT) or bioradiation (BRT) can cause early side effects like mucositis, odynophagia, dysphagia, xerostomia, orofacial pain, laryngeal radio necrosis, dermatitis, hair loss, nausea, and vomiting [3]. Those early side effects can cause inadequate nutrition and hydration, which can lead to loss of muscle mass, loss of muscle strength, increased fatigue, decreased physical performance, and a decreased quality of life (QoL) [4, 5]. Physical exercise interventions (PEIs) primarily focusing on resistance training have proven effective in enhancing various health-related, physiological, and disease specific outcomes like early side effects [5–7]. However, the existing evidence suggests that resistance training alone may not suffice. Therefore, incorporating endurance training into the regimen appears to be beneficial [7]. Endurance training can reduce fatigue, improve QoL, and improve physical function [7]. For an optimal effect of both resistance and endurance exercises, it is necessary to train on a moderate to hard load and intensity [8]. Thereby, it is of importance to set the PEI volume on the patient’s physical performance at the start to be able to adapt the exercise intensity depending on progress, deterioration, and symptom burden during the PEI.

During the last decade, 12 studies have been published investigating PEIs in patients with HNC during RT, CRT or BRT ((C/B)RT) treatment [9–20]. In ten studies [9–11,13–17,19,20], the PEI consisted of resistance exercises only, and in two studies [12, 18] both resistance and endurance exercises were part of the PEI. Two of these 12 studies were randomised clinical trials (RCTs) with a satisfying sample size [11, 18]. Hu et al. [11] included 146 patients in China. They showed shortly after CRT that a 60 min supervised resistance training twice a week during CRT decreased fatigue and improved QoL significantly [11]. Samuel et al. [18] included 148 patients in India and combined resistance exercises with endurance exercises in a 7 week supervised training five times a week followed by a 4 week home based training during CRT. In this study they showed a significant improvement on physical performance, measured by the six minutes walking test (6MWT), a fatigue decline and QoL improvement shortly after CRT.

To our knowledge, there is no cost-effectiveness analysis of a PEI for patients with HNC receiving (C/B)RT, while hospitals and insurances need this information due to the increasing financial burden of cancer care [21]. So it is of importance to investigate both the effects and cost-effectiveness of an exercise intervention in patients with HNC in a RCT. On the other hand, the challenge of recruitment often arises in RCTs. A good alternative to a RCT is the trial within cohort (TwiCs) design [22]. This is a design for pragmatic trials, which embeds a trial within a cohort [23]. This design can help to prevent unwanted recruitment problems due to a staged-informed consent (IC) [22]. Using this design, information about the intervention is provided exclusively after randomisation to the intervention group, decreasing the risk of disappointment bias or cross-over influences [22].

To measure the effect of a PEI, physical performance is an important outcome, as it is closely associated with QoL in patients with HNC [23]. In cancer rehabilitation, physical performance is frequently measured with parameters such as strength and walking ability [24]. Thereby, it has been shown that lower extremity muscle strength, as measured with the 30 s chair stand test (30CST), is associated with walking performance as measured with the 6MWT in older adults [25]. Both the 30SCT and 6MWT are commonly used and reliable measurement instruments to evaluate physical performance in patients with cancer [9]. Based on the fact that Samuel et al. [18], who used an optimal sample sized RCT with a PEI combining resistance and endurance training, used the 6MWT to objectively measure physical performance, the 6MWT was used as primary outcome in this study.

The aim of this study is to investigate and compare physical performance, muscle strength, fatigue, QoL, body mass index (BMI), nutritional status, physical activity, treatment tolerability of (C/B)RT, and healthcare related costs in patients with HNC with and without a 10 week PEI during (C/B)RT. Our hypothesis presumes that patients with HNC receiving the PEI will have less reduction in physical performance after (C/B)RT, as measured with the 6MWT, in comparison to patients not receiving this PEI.

## Methods

### Study design

A RCT is a powerful design for evaluating clinical interventions and is considered to generate a high level of evidence [26]. However, a RCT design has several limitations: patients may dislike the randomisation and therefore refuse participation. When patients are randomised for the control group but have a preference for the experimental intervention, drop-outs may occur. Those limitations have consequences for the recruitment and power of the study. To improve recruitment, in this study a TwiCs design will be used. The TwiCs design consists of an experimental intervention study within an observational longitudinal cohort. This design uses a staged-IC. Patients will be asked to participate in an observational longitudinal cohort study and will be informed about the design with the probability to be randomly invited for an experimental intervention which they can accept or refuse. After cohort enrolment, all patients will be randomised. This approach is feasible and efficient [27]. Patients who accept the experimental intervention will receive a 10 week PEI during (C/B)RT treatment.

### Participants

At least 112 patients will be recruited at Instituut Verbeeten, Tilburg, the Netherlands. This hospital is specialized in treating patients with HNC of which approximately 100 patients are treated with (C/B)RT yearly. Patients with HNC scheduled for (C/B)RT will be recruited by the radiation oncologist. First, patients will receive a letter explaining the study aims and procedures. Second, patients who have expressed their interest will be contacted by the local investigator and procedures will be explained in more detail. When a patient agrees, a baseline visit will be scheduled to obtain written IC and perform baseline evaluation measurements.

Patients treated with RT receive 30 times 2,2/2,1gray (Gy). Patients treated with CRT or BRT will receive seven times Cisplatin or Nivolumab combined with 35 times 2 Gy RT. This treatment will be adapted when necessary. All patients with HNC receive advices based on the ‘Dutch physical activity guideline’ [28]. Just before and during (C/B)RT, nutritional care is provided by a dietician on a weekly basis, focusing on optimal energy balance and prevention of negative energy balance.

### Inclusion and exclusion criteria

In order to be eligible to participate in this study, a patient must meet the following inclusion criteria: 1) patients with HNC who are scheduled for (C/B)RT, 2) ≥ 18 years of age, 3) sufficient Dutch writing and reading skills, 4) a Karnofsky performance status (KPS) > 60 [29], 5) able to walk ≥ 60 m without a mobility aid, and 6) no contraindication for physical activity as measured with the physical activity readiness questionnaire (PAR-Q) [30]. Patients who meet any of the following exclusion criteria will be excluded from participation in this study: (1) recurrence of HNC and/or (2) secondary HNC.

### Sample size

The sample size calculation is based on the primary outcome, the 6MWT. The power of the study is set on 80% (ß), using differences between two independent means with a 0.05 two-sided significance level. For calculation of the sample size, G*Power 3.1.9.2. was used [31]. Means and standard deviations (SDs) of the 6MWT of the study of Samuel et al. [19] were used. The first mean (SD) [483.16 (88.24)] is of patients with HNC who received the exercise intervention during (C/B)RT and the second mean (SD) [374.52 (110.26)] is of patients with HNC who received usual exercise care during (C/B)RT. Based on this, an effect size of 1.09 was calculated, which resulted in a sample size of 15 patients needed to undergo the PEI. We expect a drop-out of 24% as stated in the study of Samuel et al. [19]. Therefore, 20 patients need to be included in the PEI group. A feasibility study for PEI for patients with HNC in a Dutch population showed that 36% of the approached patients signed IC [13]. To include enough patients, a bigger sample size is needed. Using the expected participation percentage of 36%, a sample size of 56 is needed for the PEI group. Randomisation will be done in a 1:1 ratio so also 56 patients are needed in the control group. In total, 112 patients are needed. With the TwiCs design, two subgroups will arise in the PEI group, consisting of patients who accept and patients who refuse to undergo the PEI [26]. This type of non-compliance (refusal of the assigned treatment) will not be identical between the study arms [32]. Therefore, the sample size calculation will be revised when the real acceptance rate of the PEI differs from the initially estimated acceptance rate, before the end of the study [33].

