### Statistical analyses

To test normality of continuous data, the Shapiro-Wilk test will be used. Continuous data will be presented descriptively with means and SDs. When continuous data are not normally distributed, the median and inter quartile range (IQR) will be presented. For ordinal data, both the median and IQR will be presented. Nominal data will be presented as numbers and percentages. Comparison between normally distributed groups will be done with the independent t-test when data are normally distributed. For non-normally distributed data, the Mann-Whitney U test will be used. Nominal data will be compared by the Chi-square test or Fisher-exact test when a particular cell is < 5. For all different groups, statistical analyses will be performed for intention-to-treat (ITT) and instrumental variable analysis [47]. An interim analysis will be conducted after 26 patients underwent the PEI to evaluate the power calculation. The incremental cost-effectiveness ratio (ICER) will be calculated as the difference in costs divided by the difference in QALYs between groups. When data are missing, ‘available case analyses’ will be used, indicating that missing cases will be discarded in the variables that are needed for a specific analysis. All analyses will be performed using statistical package for the social sciences (SPSS). A *p*-value below 0.05 is considered statistically significant.

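### The 80% power stated for 112 patients does not apply to the planned ITT and IV analyses: at the plan's own 36% acceptance, ITT power is about 35–43% with 24% drop-out and 44–54% without

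*Protocol article*

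**What the plan says.** All of the sizing is in the Protocol article, Methods, Sample size.

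- Target: "The power of the study is set on 80% (ß"). The test compares two means, two-sided at the 5% level.
- Inputs for the six-minute walk: "The first mean (SD) [483.16 (88.24)] is of patients with HNC who received the exercise intervention during (C/B)RT". Usual-care patients are given a mean of 374.52 m with an SD of 110.26 m.
- Base size: "an effect size of 1.09 was calculated, which resulted in a sample size of 15 patients needed to undergo the PEI".
- Inflation: 24% drop-out takes 15 to 20. Then "Using the expected participation percentage of 36%, a sample size of 56 is needed for the PEI group", matched by 56 controls, for 112 in total.
- The section recognises that accepters and refusers will be two subgroups of the invited arm, and that refusal will not be the same in both arms. It adds that the "sample size calculation will be revised when the real acceptance rate of the PEI differs from the initially estimated acceptance rate". A reference is cited for this, but no formula is given.

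The Statistical analyses section states: "For all different groups, statistical analyses will be performed for intention-to-treat (ITT) and instrumental variable analysis [47"]. It handles missing data by available cases and plans an interim check of the power calculation once 26 patients have undergone the intervention.

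The Randomisation and blinding section provides 112 envelopes, 56 of them invitations, but also keeps the study open until 56 patients have accepted the intervention.

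**The concern.** Dividing by 0.36 corrects the number of exercisers. It does not correct the effect that the randomised comparison will show. Under ITT every invited patient counts as invited, so refusers who receive usual care pull the invited arm's mean towards the control mean. The difference shrinks in proportion to acceptance, so the required sample grows with 1/acceptance², whereas the plan uses 1/acceptance. The 80% therefore belongs to a contrast of exercisers with controls, and the protocol does not plan that contrast.

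This is the headline power for the primary outcome. A null ITT result would be read as coming from a trial with 80% power, although on the plan's own inputs its chance of detecting the assumed effect was around one half or less.

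**Working it through.** **Inputs (Sample size section).** Means (SD) 483.16 (88.24) m and 374.52 (110.26) m; two-sided 0.05; drop-out 24%; acceptance 36%; 1:1 allocation. Power is computed from the non-central t distribution for two independent means.

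**1. The plan's own figure.**
- Difference = 483.16 − 374.52 = 108.64 m.
- Pooled SD = √[(88.24² + 110.26²)/2] = 99.86 m, so d = 108.64/99.86 = 1.09.
- Power is 79% with 14 per group and 82% with 15, so n = 15.
- 15/0.76 = 19.7, rounded to 20; 20/0.36 = 55.6, rounded to 56; 2 × 56 = 112.

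The chain reproduces. Its 80% (82% at 15 versus 15) assumes that everyone in the first group exercised.

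**2. The ITT effect.** Assume that refusers have the usual-care mean and SD.
- Expected difference = 0.36 × 108.64 = 39.1 m.
- Common SD: d = 39.1/99.86 = 0.39.
- Mixture SD: the invited arm contains two subgroups with different means, so its SD = √(0.36 × 88.24² + 0.64 × 110.26² + 0.36 × 0.64 × 108.64²) = 115.3 m. Pooled with the control arm, √[(115.3² + 110.26²)/2] = 112.8 m, and d = 39.1/112.8 = 0.35.

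**3. ITT power at 56 randomised per arm, 36% acceptance.**

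| Analysed per arm | Mixture SD | Common SD |
|---|---|---|
| 56 × 0.76 ≈ 43 (24% lost in both arms) | about 35% | about 43% |
| 56 (nobody lost) | 44% | 54% |

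**4. IV power.** The IV estimate is the ITT difference divided by acceptance. Its standard error is divided by acceptance too, so the ratio hardly changes. It gains a little because the residual variance no longer contains the between-subgroup term. Simulated two-stage least squares with the mixture model gives about 39–41% with 43 per arm and 48–50% with 56 per arm.

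**5. What 80% ITT power would need.**
- At 56 per arm with 24% drop-out: acceptance of about 57% (common SD) to 63% (mixture SD).
- At 36% acceptance: 104 (common SD) to 132 (mixture SD) analysed per arm. Dividing by 0.76 gives 137 to 174 randomised per arm, or 274 to 348 in total.

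**6. The other recruitment rule.** 56 accepters at 36% means 56/0.36 = 155.6, or 156 invited, and 156 controls under 1:1 allocation. With 156 × 0.76 ≈ 119 analysed per arm, ITT power is about 76–85%. With all 156 analysed it is 86–93%.

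**The case against.** **The trial may be larger than 112.** The abstract and the Participants section say at least 112, and the rule of continuing until 56 accept would bring ITT power close to 80% or above it. So a reader should not infer that 80% is out of reach on every reading of the document. But that rule conflicts with the 56 invitation envelopes in the same section, because 56 accepters from 56 invitations requires 100% acceptance. It also conflicts with the 56 + 56 in the Sample size section. It does not support 80% at the stated 112, but it must be settled in the same correction.

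**The revision clause could repair this.** It could if acceptance differs from 36% and a suitable formula is used. It is not triggered if acceptance is as assumed. The interim check after 26 patients have undergone the intervention lies beyond the 0.36 × 56 ≈ 20 accepters expected from 56 invitations. A reader might infer that the revision would repeat the division by acceptance and so cut the sample if acceptance proves high. The document does not support that: it states no formula, its cited reference is not available here, and 112 is described as a minimum.

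**Drop-out drives the lowest figures.** This is correct. The 35–43% assumes 24% loss in both arms and should not be quoted alone; without loss the range is 44–54%. The available-case rule makes the figures with drop-out the relevant ones if the plan's 24% holds.

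**Acceptance may exceed 36%.** It may, since the 36% is consent among approached patients in a feasibility study, not acceptance among patients already in the cohort. It is nevertheless the figure the plan uses.

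**Conclusion.** The point holds for the stated size. The calculation reproduces arithmetically but powers a contrast that is not planned. At 56 per arm and 36% acceptance, no combination of the SD and drop-out assumptions brings ITT or IV near 80%: ITT has about 35–54% overall and IV about 39–50%.

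These figures rest on the plan's means, SDs, 36% acceptance and 24% drop-out. They also rest on three assumptions of this review: refusers perform like usual-care patients, drop-out is the same in both arms, and drop-out is unrelated to acceptance. The conclusion is conditional on 36% acceptance and would ease considerably if acceptance reached about 57–63%. It says nothing about which formula the planned revision will use.

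**What to change.** 1. Restate the power. At 112 patients and 36% acceptance, ITT power is about 35–43% with 24% drop-out and 44–54% with complete follow-up, and IV power is similar or slightly higher. Add that 80% at 56 per arm with 24% drop-out needs about 57–63% acceptance.
2. Replace the inflation step, and specify the same rule for any revision to the observed acceptance rate: n per arm = n(full effect) / [(1 − drop-out) × acceptance²], with the variance of the accepter/refuser mixture. Use the unrounded n(full effect), or recompute directly from the diluted difference. Starting from the rounded 15 overshoots: 15/(0.76 × 0.36²) = 152 per arm, against 137 from the direct calculation with the common SD.
3. State one recruitment target. Reconcile the 112 patients and 112 envelopes with the rule of continuing until 56 accept, and give the power for the size chosen.

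Restating the power costs only wording, and the figure becomes less favourable. Keeping 80% at 36% acceptance is not free: it means 274–348 randomised patients, or 2.7 to 3.5 years of the roughly 100 patients that the Participants section says the centre treats yearly, even if every one of them joined.

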### Randomisation and blinding

At the first appointment the radiation oncologist will provide the study information. In Fig. 1, an overview is provided of the recruitment of patients. After enough time (until one week before the start of (C/B)RT) to consider their decision, the local investigator contacts the patient and asks to participate in the cohort. When the patient agrees, a baseline measurement (M0) will be planned. At the start of this measurement appointment, the patient will sign the IC for participating in the observational longitudinal cohort study. Immediately after the baseline measurement, the data collector will randomise the patient to participate in the experimental PEI or stay in the observational longitudinal cohort. Patients who refuse to participate will be listed and asked for their reason to refuse. When a randomised patient agrees to participate in the PEI, the first appointment for the PEI will be planned. During the first PEI appointment, the IC for PEI will be signed. For randomisation, a box with 112 sealed envelopes will be used. Fifty-six envelops contain ‘invite to undergo the experimental exercise intervention’ and 56 envelopes contain ‘no invitation to undergo the experimental exercise intervention’. This study will continue until 56 patients accepted the experimental PEI. The local investigator (YK) will perform the group allocation and data collection, so this researcher will not be blinded. The physiotherapists who will provide the intervention and the patients who undergo the experimental PEI will also not be blinded.

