### Measurements

The socio-demographic data (age, gender, education, employment and marital status) and medical data (tumour site, disease stage, comorbidity, HPV status, tobacco and alcohol use, nutrition status and type of treatment) will be assessed at baseline (M0). Physical performance, muscle strength, fatigue, QoL, BMI, nutritional status, and physical activity will be assessed at baseline (M0), 12 weeks (M1) and 6 (M2) and 12 (M3) months after baseline. Treatment tolerability will be assessed at M1, M2 and M3. Health related costs will be collected at M3. All tests and Dutch questionnaires are validated and have satisfying clinimetric properties.

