## Discussion

HNC itself, but also side effects of (C/B)RT sush as inadequate nutrition, weight loss, loss of muscle mass, loss of muscle strength, fatigue, and QoL can be deteriorated by a PEI [4]. Therefore, the aim of this study is to investigate and compare physical performance, muscle strength, fatigue, QoL, BMI, nutritional status, physical activity, treatment tolerability of (C/B)RT, and healthcare related costs in patients with HNC with and without a 10 week PEI during (C/B)RT. It has been demonstrated that PEI in patients with HNC during (C/B)RT is feasible and safe, reducing the deterioration of physical performance and QoL during (C/B)RT [9–20].

This study presents various practical and operational challenges which can involve the performance of this study. Blinding of the local investigator responsible for follow-up data collection is not feasible due to the small scale of the hospital, making it apparent which patient receives the PEI and which patient does not. Consequently, the local investigator performs both randomisation and data collection, a decision aimed at enhancing participant comfort and convenience by limiting interactions to one investigator.

With the intention to prevent a potential sample bias, a diverse and inclusive cohort of patients with HNC will be selected [48]. Consequently, the population participating in this study will be subjected to a varied spectrum of treatments within (C/B)RT. This comprehensive selection is made in the pursuit of enhancing the generalizability of the findings.

In clinical practice, patients receiving (C/B)RT experience a demanding and time-consuming schedule. Their schedule includes multiple appointments with healthcare professionals, including a radiation oncologist, dietician, and dental hygienist. This high frequency of appointments may lead to refusal of study participation [12]. In an effort to accommodate and facilitate participation, we prepared a strategy to schedule study appointments just before or after a patient’s usual care appointment at Instituut Verbeeten.

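### Radiotherapy alone and chemo- or bioradiation are pooled, but neither the single envelope box nor the stated unadjusted tests use treatment type: a loss of precision, not a bias

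*Protocol article*

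**What the plan says.** **Population.** Inclusion and exclusion criteria (Protocol article) admits "patients with HNC who are scheduled for (C/B)RT", without restriction by type. Participants describes two kinds of regimen: "Patients treated with RT receive 30 times 2,2/2,1gray (Gy"), and "Patients treated with CRT or BRT will receive seven times Cisplatin or Nivolumab combined with 35 times 2 Gy RT". The Discussion presents the mix as intended, for generalisability: "the population participating in this study will be subjected to a varied spectrum of treatments within (C/B)RT".

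**Timing.** Measurements lists treatment type among the baseline data ("nutrition status and type of treatment) will be assessed at baseline (M0")). Randomisation and blinding places allocation directly after that baseline visit, so the factor is known when the envelope is drawn.

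**Allocation.** "For randomisation, a box with 112 sealed envelopes will be used", half of them inviting the patient to the exercise programme and half not. Sample size gives the ratio: "Randomisation will be done in a 1:1 ratio so also 56 patients are needed in the control group". No stratum, block or minimisation factor is named.

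**Analysis.** Statistical analyses names the t-test or Mann-Whitney test for continuous data and the chi-square or Fisher test for nominal data, under ITT and IV analysis. None of the named tests carries a covariate.

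**The concern.** Treatment type is a baseline factor that the investigators expect to vary, that is known before allocation, and that they already collect. Yet it enters neither the allocation nor the stated comparisons.

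The link is closest for some secondary outcomes. The plan counts completion of scheduled treatment, treatment adjustment, toxicity and one-year costs as outcomes. A patient on RT alone has no systemic drug to adjust, tolerate or pay for, so these outcomes depend on regimen by construction. If one arm happens to hold more chemo- or bioradiation patients, an unadjusted difference in them could be read as an effect of exercise. For the 6MWT a link is plausible, but the document gives no figure for it.

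**Working it through.** **1. The plan's own figures.** From Sample size, the 6MWT means (SD) are 483.16 (88.24) and 374.52 (110.26).
- Difference: 483.16 - 374.52 = 108.64 m.
- Pooled SD: sqrt((88.24² + 110.26²)/2) = 99.86 m. Effect size: 108.64/99.86 = 1.09.
- Two-sided t-test at 0.05: 15 per group gives 82.0% power and 14 gives 79.1%, so n = 15.
- 15/(1 - 0.24) = 19.7, so 20. 20/0.36 = 55.6, so 56. 2 × 56 = 112.

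All stated figures reproduce.

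**2. Chance imbalance in regimen.** Inputs: 112 envelopes, 56 per arm. The share on chemo- or bioradiation (CRT/BRT) is not documented; 30-50% is assumed. The number of such patients in one arm is hypergeometric (112, K, 56).

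| Assumed share | K | SD of arm difference | P(≥10 points) | P(≥15 points) | P(≥20 points) |
|---|---|---|---|---|---|
| 30% | 34 | 8.7 points | 0.30 | 0.06 | 0.02 |
| 40% | 45 | 9.3 points | 0.25 | 0.12 | 0.02 |
| 50% | 56 | 9.5 points | 0.34 | 0.09 | 0.04 |

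The figures do not rise smoothly with the share because the counts are discrete.

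**3. Effect on the primary contrast.** With 36% acceptance, the ITT difference implied by Sample size is 0.36 × 108.64 = 39.1 m. Its standard error at 56 per arm is 99.86 × sqrt(2/56) = 18.9 m. Assume that the regimens differ by 50 m in follow-up 6MWT (not documented). A 15-point imbalance then moves the ITT difference by 0.15 × 50 = 7.5 m:
- 7.5/39.1 = 19% of the implied effect;
- 7.5/18.9 = 0.4 of a standard error.

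**4. The IV estimate.** Dividing by 0.36 scales everything alike: shift 7.5/0.36 = 20.8 m, effect 39.1/0.36 = 108.6 m, standard error about 18.9/0.36 = 52 m. The ratios remain 19% and 0.4.

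**5. Gain from adjustment, 6MWT.** Between-regimen variance is p(1 - p) × gap². The total variance is 99.86² = 9,972 m², and the standard error shrinks by 1 - sqrt(1 - fraction explained).

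| Assumed gap | Variance explained, p = 0.30 to 0.50 | Reduction in standard error |
|---|---|---|
| 25 m | 131 to 156 m² (1.3-1.6%) | about 1% |
| 50 m | 525 to 625 m² (5.3-6.3%) | about 3% |
| 100 m | 2,100 to 2,500 m² (21-25%) | 11-13% |

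No such figure can be derived for toxicity, treatment adjustment or cost, because the document gives no values for them by regimen.

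**The case against.** **Simple randomisation is valid.** A single box with fixed 56/56 totals gives a fair comparison, and the unadjusted standard error already allows for chance imbalance. This stands. A reader might infer that the ITT result is biased or its type I error raised; the documents do not support that.

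**The IV estimate is not especially vulnerable.** A reader might infer that dividing by acceptance magnifies the problem. Step 4 shows that effect, shift and standard error scale together. Nor would a link between regimen and acceptance bias the IV estimate, since the instrument is the randomised invitation.

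**The size for the 6MWT is modest and assumed.** Neither the regimen share nor the 50 m gap is documented, and nothing in the article says that regimen predicts walking distance. It cannot be called a known prognostic factor for the primary outcome. This stands too.

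**The final sample size is not settled.** Randomisation and blinding also says recruitment runs until 56 patients have accepted. At 36% that needs 56/0.36 = 156 invitations and about 312 patients, where the chance of a 10-point gap falls to about 6-9%. Against "In total, 112 patients are needed" and a 112-envelope box, that sentence needs reconciling in its own right. The figures here hold for 112.

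**Covariates may be in an unseen analysis plan.** That is possible, and silence in an article would be no finding. The point rests on what the article does state: the tests it names take no covariate, so a covariate-adjusted primary analysis would depart from the published plan.

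**Stratified blocks have a cost.** One unblinded investigator allocates and collects data. In small blocks the last assignment is certain once the others are known, so two blocked strata are easier to predict than one large box. This is why stratification is not the main recommendation.

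**Conclusion.** The plan leaves a recorded pre-randomisation factor unused in a trial that pools regimens on purpose. The consequence is lost precision and a less credible single result if the arms happen to differ; the validity of the comparison is not in question. An imbalance of 10 points or more is fairly common (25-34%), one of 15 points or more less so (6-12%), and one of 20 points or more uncommon (2-4%), all for 112 patients and an assumed 30-50% CRT/BRT share. For the 6MWT, adjustment is worth about 3% of the standard error under the assumed 50 m gap. The stronger reason to adjust lies with toxicity, treatment adjustment and cost, where dependence on regimen follows from the regimens themselves, although its size cannot be given. This is a worthwhile, inexpensive improvement rather than a defect that undermines the trial.

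**What to change.** In Statistical analyses, replace the unadjusted two-group comparisons with regression models: linear for the 6MWT, and models suited to the outcome type elsewhere. Prespecify treatment type (RT alone versus CRT/BRT) as a covariate in both the ITT and IV analyses, together with the baseline value of the outcome where it is measured. Define treatment type as planned at M0, not as received, because treatment adjustment is itself an outcome. In the IV analysis the covariates belong in both stages.

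The cost is a few sentences and one or two model parameters. No new data are needed, and the change can be made after recruitment has begun, provided it is fixed before outcomes are examined by arm.

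Stratifying the envelopes by treatment type is optional. With two series in blocks of four, each stratum could be off by at most 2 patients, capping the difference at about 3.6 points (for example 29/56 versus 27/56). If it is adopted, use concealed blocks of varying size, preferably prepared and held by someone other than the investigator who enrols and measures patients.
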